### Health and Demographic Surveillance Systems: A Solution

Health and demographic surveillance systems (HDSSs) provide continuous, longitudinal, population-based measurement of demographic, health, and social indicators within geographically defined populations [20,21]. HDSSs conduct regular household visits at intervals of 4 to 12 months, systematically updating births, deaths, migrations, and health events for all residents, enabling accurate calculation of rates and individual-level tracking over time [22]. This longitudinal design allows incidence assessment, prospective risk factor identification, intervention evaluation, and temporal trend monitoring that are impossible with cross-sectional surveys [15].

HDSSs differ fundamentally from other surveillance approaches in ways directly relevant to NCD monitoring. Unlike facility-based surveillance that captures only health care–seeking individuals, HDSSs conduct active community-based surveillance reaching all residents regardless of care-seeking behavior, health status, or socioeconomic position [11]. Unlike sentinel systems that monitor selected populations or facilities, HDSSs provide comprehensive data for entire defined populations, enabling unbiased prevalence and incidence estimation [23]. Unlike DHS, which provides periodic snapshots, HDSSs generate continuous real-time data enabling detection of emerging trends and rapid public health response [24].

Concrete examples demonstrate HDSS value for NCD surveillance. Verbal autopsies conducted in 6 eastern and southern African HDSSs revealed stable NCD mortality rates from 1995 to 2019 despite substantial declines in communicable disease mortality—epidemiological patterns that would be invisible to episodic cross-sectional surveys [25]. In rural South Africa, HDSS data showed that life-years lost to NCDs exceeded pre-HIV epidemic levels by 2014‐2018, demonstrating the system’s capacity to detect critical epidemiological transitions and inform policy priorities [19].

HDSSs employ standardized instruments ensuring data comparability across sites and over time [21], maintain population-based sampling frames covering all residents [20], and integrate multiple data sources, including household surveys, health facility records, and vital events registration [26]. They serve as platforms for nested studies, randomized trials, and intervention evaluations [27], generating evidence directly applicable to policy and practice.

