### Follow-Up Procedures

Following the baseline census, longitudinal data collection rounds will be implemented annually over the 5-year surveillance period. Using the existing household and individual registers, field teams revisit each HHID and reverify the household roster, updating entries for births, deaths, in-migrations, out-migrations, and changes in marital status. Migration events are classified and dated using standard HDSS definitions, enabling calculation of person-time at risk and net migration rates. Migration events are identified and documented during each annual household roster update. New residents found in a previously mapped household who meet the standard residency criterion (at least 3 of the last 6 mo or intending to stay at least 6 mo) are classified as in-migrants, assigned a unique individual ID, and enrolled prospectively, with their origin and date of arrival recorded. Previously enrolled individuals confirmed by household members to have permanently departed the HDSS ward boundaries are classified as out-migrants, with their date of departure, destination, and reason for migration recorded and their follow-up record closed from that date, contributing person-time up to departure. Individuals who return after out-migration are reenrolled under their original ID, ensuring longitudinal continuity.

At each round, eligible adults are recontacted for updated interviews and measurements to estimate NCD prevalence and incidence, monitor changes in health-related behaviors and attitudes, and track risk factors over time. All recorded deaths are subjected to verbal autopsy using the WHO 2016 [31] standardized instrument administered on tablets; data are processed with automated cause-of-death assignment tools (eg, InterVA or InSilicoVA), given the limitations of vital registration in this setting.

Participant retention is managed through a structured recontact protocol whereby temporarily absent individuals receive at least 2 repeat visits at different times before being recorded as noncontactable for that round. At each round, the baseline characteristics of participants lost to follow-up will be compared with those retained to assess and account for potential attrition bias.

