## Results

The Zimbabwe HDSS was granted ethical approval by the Medical Research Council of Zimbabwe on July 30, 2024. Community profiling and household mapping were completed in both sites in the third quarter of 2024. Baseline data collection was completed in Mt Darwin (rural site) in December 2024 and in Bindura (urban site) in March 2025. Data cleaning and quality assurance procedures for the baseline dataset were initiated in April 2025, and statistical analysis of baseline prevalence, risk factor distributions, and rural-urban comparisons is projected for completion by the first quarter of 2026, with findings expected to be submitted for publication by the end of 2026. The first annual longitudinal follow-up round is planned for the second quarter of 2027, subject to funding availability. Subsequent follow-up rounds are scheduled annually through 2029, with longitudinal incidence estimates, demographic event rates, and NCD trend analyses expected to be published progressively from 2026 onward.

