### Future Plans

Future plans for the HDSS include the continuation of biannual longitudinal follow-up rounds over a 5-year period to monitor the incidence and prevalence of common NCDs and update data on key risk factors and social determinants. Efforts will focus on analyzing trends in births, deaths, migration, and health-related behaviors to understand shifts in NCD patterns within rural and urban contexts. The long-term strategic trajectory of the HDSS includes plans to incrementally expand the geographic coverage to incorporate additional rural and urban wards. This expansion aims to enhance the system’s capacity to capture broader regional variations and longitudinal shifts in NCD burden.

Mt Darwin (rural) and Bindura (urban) were purposively selected as typical districts within Mashonaland Central Province, reflecting common rural agricultural and urban mixed-economy contexts and existing collaborations with the Ministry of Health and Child Care and the University of Zimbabwe. This initial phase is therefore designed to establish a feasible dual-site HDSS that captures the primary contrast between rural and urban settings, rather than to be statistically representative of all rural or all urban districts nationally. To address this limitation, future phases of the HDSS are planned to extend surveillance to additional rural and urban districts in Zimbabwe, thereby widening geographic coverage and enabling assessment of variation within rural areas and within urban areas, as well as between them.

Future activities will also focus on integrating new, specialized modules dedicated to capturing data on environmental exposures, performing comprehensive mental health assessments, and facilitating more detailed NCD phenotyping. The HDSS aims to expand geographic coverage to include additional districts for broader regional representation. New data collection modules will be incorporated to capture environmental exposures, detailed mental health assessments, and refined NCD phenotyping. These activities will enable robust rural-urban comparisons and provide evidence to guide targeted public health policies and interventions, particularly for vulnerable populations.

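### Follow-up is called yearly and also biannual, yet the first round falls 25 to 30 months after baseline, so the first contrast is not an annual change and remeasured incidence cannot appear from 2026

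*Protocol article*

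**What the plan says.** The protocol article gives the follow-up frequency in several places, and they do not agree.

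- The Methods part of the Abstract has follow-up every year. Follow-Up Procedures says "longitudinal data collection rounds will be implemented annually over the 5-year surveillance period".
- Future Plans instead describes "the continuation of biannual longitudinal follow-up rounds over a 5-year period".
- The Results section dates the work: "Baseline data collection was completed in Mt Darwin (rural site) in December 2024", and "in Bindura (urban site) in March 2025". It continues: "The first annual longitudinal follow-up round is planned for the second quarter of 2027, subject to funding availability". After that, "Subsequent follow-up rounds are scheduled annually through 2029". The Results part of the Abstract gives the same dates.
- The sentence in Results that schedules the later rounds has longitudinal incidence estimates, demographic event rates and "NCD trend analyses expected to be published progressively from 2026 onward". The Abstract gives 2026 to 2029 for incidence and trends.

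Three other sections depend on the interval. Study Population and Sampling sizes the longitudinal comparison on a two-point absolute change per year between rounds, illustrated as 30% to 32%. Follow-Up Procedures obtains NCD incidence by recontacting and remeasuring adults at each round. Data Collection Methods has each household visit record births, deaths and migrations that occurred after the previous one.

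**The concern.** Visit frequency is a defining design parameter of a surveillance cohort. Here it has two stated values, and the dates deliver neither in the first interval. The second aim is to characterise incidence and temporal trends, and the article criticises the Demographic and Health Surveys for the gaps between their rounds, so a reader will take the yearly interval as a property of the data.

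If the text stands, three things can go wrong. A change between baseline and 2027 may be read as one year's change. Readers and policymakers are promised longitudinal results in a year when no second measurement exists. And demographic events in the first interval may be presented as if captured by yearly visits, when they rest on much longer recall.

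**Working it through.** **1. Frequency.** Biannual normally means twice a year. If every two years was meant, it still conflicts with the yearly commitment in the Abstract and Follow-Up Procedures, and with annual rounds from 2027 to 2029 in Results. No reading of the word reconciles the sections.

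**2. First interval.** Inputs: the completion month at each site (Results) and the second quarter of 2027, taken as April to June.

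- Mt Darwin: December 2024 to April 2027 = 28 months; to June 2027 = 30 months.
- Bindura: March 2025 to April 2027 = 25 months; to June 2027 = 27 months.

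Overall this is 25 to 30 months, or 25/12 = 2.1 to 30/12 = 2.5 times a 12-month interval. Baseline start dates are not given. People measured before the completion month wait longer, so these are the shortest intervals for each revisit date.

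**3. Number of rounds.** A first round in 2027 and annual rounds through 2029 give three: 2027, 2028 and 2029. The first is conditional on funding, so three is a maximum.

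**4. The sample-size target.** The stated figure that rests on a yearly interval is about 3500 per site per round, for 30% against 32%, 80% power and two-sided alpha 0.05. The usual formula for two independent proportions is

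n = [1.96 × √(2 × 0.31 × 0.69) + 0.842 × √(0.30 × 0.70 + 0.32 × 0.68)]² / 0.02² ≈ 8394 per round,

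so 3500 is not reproduced this way. That is a separate matter, and nothing below depends on it. What matters here is the contrast the target describes. With a steady true rise of 2 points a year, the difference between baseline and the first round is 2 × months/12:

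| Months | Expected difference (points) | Yearly rate equivalent to an observed 2-point difference |
|---|---|---|
| 25 | 4.17 | 24/25 = 0.96 |
| 27 | 4.50 | 24/27 = 0.89 |
| 28 | 4.67 | 24/28 = 0.86 |
| 30 | 5.00 | 24/30 = 0.80 |

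The first contrast is thus about 30% against 34.2% to 35.0%, not 30% against 32%.

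**5. Publication from 2026.** The earliest remeasurement is April 2027, 4 months after December 2026. NCD incidence and trends need two measurements, so only baseline results can appear in 2026.

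**6. Event capture.** At the first follow-up the look-back to the previous visit is at least 25 months in Bindura and 28 in Mt Darwin. An in-migrant who arrives after baseline and leaves before the 2027 round is not measured.

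**The case against.** The delay is disclosed and tied to funding. It is operational, not a concealed analytic error, and the remedy is mostly wording. The 2027 to 2028 and 2028 to 2029 intervals can still show yearly change, so the sample-size target applies to two of the three intervals. All of this stands, and it confines the point to the first interval and to statements not brought into line with the dates.

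Several stronger readings are tempting, but the article does not support them.

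- *The trend tests treat 25 to 30 months as 12.* Data Analysis plans chi-square tests for trend over time without naming the time score, and does not say round number. It also plans survival analyses, and Data Management bases rates on person-time. The risk is open, not stated.
- *Short-stay migrants are never seen.* Household forms record migrations between visits, and Follow-Up Procedures dates them. Such people are unmeasured but may still be reported by those who remain. The article gives no departure rate, so I put no size on this.
- *The study breaks its own visit standard.* The Introduction's "HDSSs conduct regular household visits at intervals of 4 to 12 months" is general background. This study's commitment is yearly rounds.
- *The rural interval is about 3 months longer.* That assumes simultaneous revisits, which is not stated. On completion dates the difference could run from 28 − 27 = 1 month to 30 − 25 = 5 months.
- *Power is lost.* The reverse is true for the first contrast: a steady 2-point yearly rise accumulates and is easier to detect. The fault is that the contrast is mislabelled.
- *No yearly rate can be given for 2025 to 2027.* This holds for conditions measured only at rounds. Dated births, deaths and migrations can be tabulated by calendar year, subject to recall error.

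**Conclusion.** The point holds as an error in the current text. The follow-up frequency contradicts itself. The first round comes 28 to 30 months (Mt Darwin) and 25 to 27 months (Bindura) after baseline completion, and at most three follow-up rounds fit. The yearly change used for sample size does not describe the first contrast, where it would appear as about 4.2 to 5.0 points, and remeasurement-based incidence and trends cannot be published from 2026.

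The month counts assume an April to June 2027 round and start from completion dates; earlier enrolment or a funding delay lengthens them. The 4.2 to 5.0 points assume a steady rise of 2 points a year. Some demographic rates might in principle come from recall at baseline, but the article describes no such analysis, and this would not supply NCD incidence.

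**What to change.** - Bring the Abstract, Follow-Up Procedures, Results and Future Plans to one schedule. On the stated dates that is baseline plus rounds in 2027, 2028 and 2029.
- For longitudinal NCD incidence and trends, replace 2026 with a date after the 2027 round. Baseline prevalence can keep its own date.
- Express change per year from actual interview dates, so that the trend tests in Data Analysis reflect the unequal intervals. State that the two-point yearly target refers to the 12-month intervals, or restate it for the first one.
- For conditions measured only at rounds, report one period-average rate from baseline to 2027.
- State that vital and migration events in that interval rest on recall of more than two years and that short-stay in-migrants are not measured. Dated demographic events may still be reported by calendar year with this caveat.

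The cost is changed wording and use of interview dates. No extra data are needed. The downside is a less ambitious claim for the first interval.

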## Discussion

### Anticipated Contributions and Impact

The establishment of a comprehensive HDSS encompassing both rural and urban locales in Mashonaland Central Province is poised to yield findings with transformative potential for public health policy, program design, and research [32,33]. This system’s fundamental contribution lies in its capacity to generate high-quality, longitudinal data necessary for the monitoring of NCDs, migration, and demographic events—a critical gap currently present in Zimbabwe’s routine health information infrastructure [34]. Unlike cross-sectional surveys, the systematic, repeated population-based data collection permits the detection of subtle, emerging health trends and the robust monitoring of persistent socioeconomic inequalities over time [10,35].

A defining methodological asset is the dual-site, rural-urban design (Mt Darwin and Bindura). This design facilitates direct, empirical comparisons, providing nuanced evidence on how geographical context, migration patterns (including circular migration), and social determinants interact with NCD risk and disease progression [36,37]. For instance, the platform can contrast rural challenges—such as restricted access to medical care and delayed diagnosis—against urban epidemiological profiles, which often exhibit faster lifestyle transitions, increased environmental risk exposures, and elevated rates of obesity or metabolic syndrome [36]. The inclusion of dedicated modules covering behavioral risk factors, health care utilization, and cause-specific mortality via verbal autopsy ensures that emerging NCD patterns are thoroughly contextualized [38,39]. The digital platforms employed, featuring real-time data validation and immediate uploads, ensure both timeliness and the capability to respond rapidly to local public health priorities [40,41].

The intrinsic flexibility of the HDSS model provides a robust infrastructure for launching nested substudies and facilitating specialized research modules [10]. This adaptability allows for targeted investigation into specific NCD phenotypes or vulnerable age cohorts and supports the future establishment of a biobank for advanced biomarker and genetic studies, all anchored within the longitudinal cohort framework [37]. Critically, the potential for linking real-world surveillance data with facility-level health records addresses a current research challenge, enabling longitudinal evaluation of care quality, patient trajectories, and overall health system performance—outcomes typically inaccessible through standard administrative datasets alone [42,43].

A substantial anticipated contribution involves focusing research attention on the social and economic determinants of NCD outcomes, particularly how these factors differ and intersect across the rural-urban continuum [37]. By tracking variables such as educational attainment, occupational status, intrahousehold conditions, and individual and household migration, the HDSS will generate pivotal insights into identifying the most vulnerable demographic groups, pinpointing areas of unmet health need, and understanding how environmental conditions (eg, water and sanitation) and socioeconomic disadvantages influence NCD risk [44,45]. This evidence is paramount for guiding equitable, sustainable public health responses in rapidly urbanizing districts where new health inequities emerge due to constant population mobility [46].

The success of this HDSS is intrinsically tied to its ongoing engagement with local communities, health authorities, and key stakeholders in both rural and urban settings [47]. The methodological reliance on participatory approaches ensures that surveillance findings are communicated in accessible formats and, importantly, that community input is actively integrated to shape subsequent research priorities and data collection efforts [47]. Structured community engagement mechanisms, including site-specific Community Advisory Boards, postround community feedback meetings, and preround formative assessments, ensure that community input actively shapes data collection methods, dissemination formats, and research priorities. These participatory mechanisms are distinct from the formal institutional collaborations (described below) with academic, government, and health system partners, which focus on scientific, technical, and policy objectives. This creation of continuous feedback loops enhances the practical relevance, acceptability, and credibility of the evidence, fostering a sense of shared responsibility necessary for translating surveillance findings into local policy and practice [48,49]. Ultimately, by fostering strong collaborative ties across academic institutions, government bodies (including the Ministry of Health and Child Care), and health care providers, the HDSS aims to serve as a regional model for policy-responsive, sustainable, and ethically sound surveillance, building the local capacity necessary to accelerate Zimbabwe’s path toward universal health coverage and the Sustainable Development Goals [50,51].

### Strengths and Limitations

The principal strengths of this rural-urban HDSS lie in its inherent methodological design, which provides longitudinal, context-rich insights into the dynamics of NCDs across contrasting environments. The systematic, repeated tracking of vital events, disease trends, and risk factors, employing harmonized, standardized methods in both rural and urban settings, facilitates robust comparisons of health transitions and allows for the differential assessment of intervention impacts—capabilities that fundamentally distinguish it from conventional cross-sectional designs. Comprehensive enumeration, coupled with proactive community engagement within distinct environments, alongside the application of validated digital data collection tools (REDCap), ensures the acquisition of high-quality, relevant longitudinal information. This dual-site structure is particularly valuable for identifying emerging health disparities, enabling the tailoring of evidence-based public health responses specific to each context and significantly enhancing the system’s contribution to multisite analytic collaborations and sustainable research capacity development in Zimbabwe.

Nevertheless, this intensive methodological approach presents several limitations that demand vigilant management. The purposive selection of surveillance sites, designed to capture key rural and urban contrasts, means that the findings may not achieve full generalizability to Zimbabwe’s highly heterogeneous national population or to other heterogeneous regions. Ongoing operational challenges include managing participant attrition, particularly loss to follow-up, which may be exacerbated in mobile urban or periurban populations, and navigating the complexities inherent in conducting intensive longitudinal surveys across diverse community settings. The current protocol captures mobile phone ownership and network availability as basic proxy indicators of digital access; however, it does not comprehensively assess digital readiness, including smartphone penetration, broadband affordability, charging infrastructure, or internet literacy. Given the rapidly evolving digital landscape in Zimbabwe, including the emergence of satellite-based internet services and the growing use of connected devices for chronic disease self-management, a more comprehensive digital readiness module is planned for incorporation in future surveillance rounds. Furthermore, the considerable resource demands necessary for sustaining the dual-site system, alongside potential risks related to self-report bias concerning sensitive health behaviors and the necessity of maintaining stringent data security protocols across disparate environments, represent significant constraints. Self-report bias for sensitive health behaviors (including sexual behavior, alcohol consumption, and mental health) remains a methodological constraint of interviewer-administered surveys. Evidence from randomized trials demonstrates that Audio Computer-Assisted Self-Interviewing (ACASI) significantly reduces social desirability bias for sensitive topics in longitudinal research [52,53]. Our study will offer literate participants the option to read selected sensitive questions on the tablet and enter their responses directly rather than responding orally to the interviewer. This partial self-administered approach is intended to reduce response bias for sensitive topics, although it is not a full ACASI implementation. Resources permitting, we plan to expand the use of self-administered or ACASI-style modules in future rounds to further reduce self-report bias. Through careful methodological stewardship and adherence to established data quality management procedures, the HDSS is positioned to mitigate these limitations, providing a robust platform for context-sensitive evidence generation.
